### Data collection

2.6

#### Assessment measures

2.6.1

For each participant, we will collect basic demographic data (eg, age, sex, years of education), comorbid-disease data that includes vascular risk factors (eg, hypertension, diabetes mellitus, ischemic heart disease, atrial fibrillation, hyperlipidemia, smoking, and alcohol use), medication history, body mass index, and family history of dementia or stroke. All participants will have 3.0-T magnetic resonance imaging (MRI) performed within 1 week of their acute cerebral infarction at the site where it was originally treated. Laboratory tests, including apolipoprotein E genotyping, will be performed before the baseline studies. MRI and MR angiographic imaging resulting from the acute cerebral infarction event will be acquired from each hospital where participants were treated. Included images will be from axial T1-weighted, T2-weighted, T2-weighted fluid-attenuated inversion recovery, diffusion-weighted, gradient-recalled echo, susceptibility-weighted, and coronal T1 sequence imaging, as well as images of intracerebral and extracerebral vessels. We will investigate the location and size of each acute cerebral infarction. We will also evaluate the degree/level of white-matter hyperintensities, the number of lacunes, the number of microbleeds, and the grade of medial-temporal atrophy. For evaluation discrepancies, these will be resolved by investigator consensus. Patient stroke-severity will be assessed at admission using the National Institute of Health Stroke Scale,^[16]^ and the modified Rankin scale. For each patient, we will additionally determine a Hachinski ischemic score^[17]^ and a Trial of ORG 10172 in Acute Stroke Treatment classification^[18]^ for stroke workup.

We will use the informant questionnaire on the cognitive decline in the elderly (IQCODE)^[19]^ to compare a patient's performance after acute infarction with that before the infarction using the information provided by a patient's caregiver. To evaluate participant cognition, we will perform baseline assessments using the Korean Mini-Mental State Examination (K-MMSE),^[20]^ the Korean version of the Montreal Cognitive Assessment (MoCA-K),^[21]^ the CDR, the Global Deterioration Scale,^[22]^ the Korean Instrumental Activities of Daily Living,^[23]^ the Geriatric Depression Scale-short form,^[24]^ and the Literacy Independent Cognitive Assessments or the Seoul Neuropsychological Screening Battery assessments.

The K-MMSE, MoCA-K, CDR, Global Deterioration Scale, and Geriatric Depression Scale-short form will be repeated at 6 and 12 months as follow-up assessments.

#### Brain positron emission tomography (PET) examination & imaging acquisition

2.6.2

All participants will undergo ^18^F-flutemetamol (FTM) positron emission tomography (PET) at baseline and be observed for 1 year regardless of the results in FTM PET. They will receive an intravenous injection of approximately 185 MBq ^18^F-FTM as a bolus, with the PET scan performed approximately 1 hour postinjection. Each participant's amyloid images will be reviewed first by a nuclear medicine physician at each imaging site and visually rated as either Aβ negative (A−) or positive (A+). Then, all amyloid imaging will be reviewed by a second nuclear-medicine physician, blinded to any clinical information, and categorized visually as either A− or A+. To confirm inter-rater reliability, we will compare the imaging-site results with those of the blinded reviews. In cases of discrepancies between classifications, they will be resolved through consultation with an additional expert.

#### Data collection methods and management

2.6.3

All paper consents will be secured in the locked cabinet. All the clinical data will be extracted from electronic medical records and checked. Data will be processed de-identified and will be recorded on standardized electronic case report forms.

### Study outcomes

2.7

The primary outcome measure will be to compare K-MMSE assessment changes (from baseline to week 52) between groups A+ and A− (determined by the visual rating of amyloid PET). The secondary outcome measures will be to compare the A+ and A− groups for differences in the conversion rate to dementia and for changes in MoCA-K assessments (from baseline to week 52). In addition to the clinical factors related to progression, we will investigate the various factors related to amyloid positivity including the IQCODE, as well.

### Sample-size estimates

2.8

We assumed that a 2-point difference in K-MMSE assessment scores (the primary outcome measure between the A+ and A− groups) after 12 months would be significant. With an alpha value set at 0.05, a beta value of 0.8 (80% power), and a standard deviation value of 5 for change, a total of 78 participants were required for each study group. Assuming a discontinuation rate of 20% during the 12-month study, the total calculated sample size required for the study was 196 participants.

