### Statistical analysis

2.9

We will either apply independent *t* tests for normally distributed continuous variables, the Mann–Whiney *U* test for non-normally distributed variables, or a chi-squared test for categorical variables to compare the 2 participant groups. Linear mixed models will be used to compare any changes in K-MMSE and MoCA-K scores between the A− and A+ groups with age, sex, and education as covariates. A chi-squared test will be used to compare conversion-to-dementia prevalence between the A− and A+ MCI groups, but Fisher exact test will be used if >20% of the values are <5.

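### The 78 per group is a one-sided sample size with no one-sided test declared; at two-sided 0.05 the stated 80% power is about 70%

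*Protocol article*

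**What the plan says.** Section 2.8 of the protocol article sizes the study on the primary outcome, the 12-month change in K-MMSE in amyloid-positive (A+) and amyloid-negative (A−) participants. It takes a 2-point difference as the target and continues: "With an alpha value set at 0.05, a beta value of 0.8 (80% power), and a standard deviation value of 5 for change". From this it concludes that "a total of 78 participants were required for each study group", and it raises the total to 196 for 20% discontinuation. Sidedness is not mentioned.

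Section 2.7 gives the comparison no direction: "The primary outcome measure will be to compare K-MMSE assessment changes", between A+ and A−. Section 2.9 plans t, Mann–Whitney, chi-squared and Fisher tests, and for the primary outcome states: "Linear mixed models will be used to compare any changes in K-MMSE and MoCA-K scores between the A− and A+ groups". None of these is described as one-sided.

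**The concern.** An alpha of 0.05 stated without qualification, next to standard two-group tests and a comparison without direction, will be read as two-sided. Under that reading the published sample size does not deliver the published power.

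This calculation is the only justification given for the study's size. The Introduction describes earlier results on amyloid and poststroke cognitive impairment as mixed, and the Discussion expects the findings to help set standards for using acetylcholinesterase inhibitors. A null primary result would be taken as evidence against a 2-point amyloid effect from a study with 80% power, when the design calculation implies about a 30% chance of missing that effect.

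There is a risk in the other direction too. If sidedness is left open and a one-sided test is chosen once data are in hand, the false-positive rate in the favoured direction is 5%, against 2.5% for a two-sided 0.05 test.

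**Working it through.** **Inputs, all from 2.8:** difference δ = 2 points; SD of change σ = 5 (standardised effect 2/5 = 0.4); alpha 0.05; power 80%; 78 per group; discontinuation 20%; total 196. Sidedness is not given, so both versions were computed.

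**Sample size per group**, normal approximation: n = 2(z_α + z_0.80)²σ²/δ², with σ²/δ² = 25/4 = 6.25.

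- One-sided: 2 × (1.645 + 0.842)² × 6.25 = 77.3, so 78. The noncentral t calculation gives 77.97, so 78. This reproduces the protocol's figure.
- Two-sided: 2 × (1.960 + 0.842)² × 6.25 = 98.1, so 99. The noncentral t calculation gives 99.08, so 100.

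The choice between normal and t moves the answer by about one participant per group, so it cannot explain the gap of 22 (100 − 78).

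**Power at 78 per group.** The standardised difference is 0.4 × √(78/2) = 2.498.

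| Test at 0.05 | Normal approximation | Noncentral t |
|---|---|---|
| One-sided | Φ(2.498 − 1.645) = 80.3% | 80.0% |
| Two-sided | Φ(2.498 − 1.960) = 70.5% | 69.9% |

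**Difference detectable with 80% two-sided power at 78 per group:** (1.960 + 0.842) × 5 × √(2/78) = 2.24 points by the normal approximation, 2.26 by t. Equivalently, to keep δ = 2 the SD would have to be about 4.46 (normal) or 4.43 (t). The protocol states neither alternative.

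**Discontinuation step:** 78/0.8 = 97.5, rounded up to 98 per group; 98 × 2 = 196. This agrees with the protocol. For reference, the two-sided requirement would be 100/0.8 = 125 per group, or 250 in total.

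**Beta:** power = 1 − β, so 80% power means β = 0.2. The stated 0.8 is the power.

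**The case against.** The strongest reply is that nothing in 2.8 is miscalculated. Every figure there follows from one consistent setting, a one-sided 0.05 test, and only the word is missing. The Discussion does state a directional hypothesis, that amyloid deposition may bring faster progression, so a one-sided intention is plausible. The article is also condensed, and sidedness may be given in a fuller document. All of this bears on what was intended. But a directional hypothesis is not a declared one-sided test. If a fuller document specifies two-sided tests, the 70% is confirmed; if it specifies one-sided tests, 2.8 and 2.9 still need to say so.

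A second reply is that 70% describes an unadjusted t test on completers, whereas 2.9 plans a mixed model adjusted for age, sex and education, with K-MMSE measured at baseline, 6 and 12 months. Such a model may recover power. If covariates explained about 20% of the variance (an assumed figure, not in the protocol), power would return to about 79%. That limits how firmly 70% can be claimed for the final analysis. It does not rescue 2.8, which takes no credit for adjustment or repeated measures and gives no correlation. Likewise, 98 evaluable per group would give 79.6% two-sided power, but the plan itself assumes 20% are lost.

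A third point is that amyloid status is observed, not allocated, so equal groups cannot be guaranteed. This is correct, and it makes 70% the best case for 156 completers. At an assumed A+ share of 40%, 30% or 20% (the protocol gives none), two-sided power is about 68%, 62% or 51%. The restated power should therefore be conditional on equal groups.

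**Conclusion.** The concern holds. With the protocol's own inputs, 78 per group gives 80% power only for a one-sided 0.05 test, and no such test is declared. At two-sided 0.05 the power is 69.9%, about 10 percentage points below the stated value, and 80% power is reached only for a difference of 2.26 points. Either the power statement is wrong under the ordinary reading of alpha, or it depends on a one-sided error rate that readers are not told about.

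The 70% rests on a two-sample t test, SD 5, and 78 completers in each group. The inflation to 196 is correct. The beta label is a minor slip. Because this is the sole power claim for the primary outcome, it needs correcting even though nothing else in the design changes.

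**What to change.** Keep N at 196 and restate 2.8 along these lines:

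> With 78 completers in each group, a two-sided alpha of 0.05 and an SD of change of 5, power is 70% for a 2-point difference and 80% for a 2.26-point difference (beta 0.2), if the two groups are of equal size.

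If a one-sided 0.05 test was truly intended, declare it in both 2.8 and 2.9 before any outcome is seen, and correct beta to 0.2 there as well. The two-sided restatement is the safer choice, because it fits the undirected comparison in 2.7 and the tests named in 2.9.

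The cost is wording only. Recruitment and procedures do not change; the price of the two-sided restatement is a less favourable stated power.

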### Statistical analysis

2.9

We will either apply independent *t* tests for normally distributed continuous variables, the Mann–Whiney *U* test for non-normally distributed variables, or a chi-squared test for categorical variables to compare the 2 participant groups. Linear mixed models will be used to compare any changes in K-MMSE and MoCA-K scores between the A− and A+ groups with age, sex, and education as covariates. A chi-squared test will be used to compare conversion-to-dementia prevalence between the A− and A+ MCI groups, but Fisher exact test will be used if >20% of the values are <5.

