### Study design

2.1

This cognitive decline according to amyloid uptake in patients with PSCI study is designed to be a prospective, multicenter, observational, and hospital-based cohort study using patients suffering from cognitive impairment (CI) after acute stroke. Participants diagnosed with either amnestic mild cognitive impairment (MCI)^[10]^ or mild dementia compatible with Diagnostic and Statistical Manual of Mental Disorders-fourth edition criteria^[11]^ after acute cerebral infarction will be consecutively recruited through 11 hospital neurology clinics. The flow chart of the study was shown in Figure 1.

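### Conversion to dementia is compared between non-randomised amyloid groups without the age, sex and education adjustment that the plan gives its other outcomes

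*Protocol article*

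**What the plan says.** Section 2.1 describes the study as "designed to be a prospective, multicenter, observational, and hospital-based cohort study". Section 2.7 compares A+ with A− participants, a status "determined by the visual rating of amyloid PET", so nothing in the design balances the two groups.

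Section 2.7 also makes conversion a named secondary outcome: "The secondary outcome measures will be to compare the A+ and A− groups for differences in the conversion rate to dementia".

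Section 2.9 then fixes the methods:

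- **K-MMSE and MoCA-K change:** linear mixed models comparing the A− and A+ "groups with age, sex, and education as covariates".
- **Conversion to dementia:** "A chi-squared test will be used to compare conversion-to-dementia prevalence between the" A− and A+ MCI groups. The fallback is stated too: "Fisher exact test will be used if >20% of the values are <5".

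No regression, stratified or time-to-event method is named for conversion. Section 2.7 mentions studying clinical factors related to progression, but it names no model and does not link that work to the A+ versus A− comparison of conversion.

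**The concern.** By its choice of covariates, the plan treats age, sex and education as differences that must be taken out before A+ and A− are compared on cognitive scores. The next sentence compares the same kind of groups on conversion and takes out none of them. The reasons for adjusting do not disappear when the outcome becomes binary.

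Eligibility runs from 60 to 85 years (section 2.3), which leaves room for the groups to differ in age. If A+ participants are older on average and older participants convert more often, a crude 2×2 table attributes part of the age effect to amyloid. The study would then report adjusted results for two outcomes and a crude result for the third. These answer different questions and could appear to disagree, or to agree, for reasons unrelated to amyloid. The Discussion expects the results to inform prediction of decline by amyloid status, so the conversion result is likely to be read as an amyloid effect.

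**Working it through.** **Figures in the plan.** There is none to reproduce. The documents state no conversion rate, MCI count, A+ share, age gap or age effect. The sample size in section 2.8 concerns K-MMSE only.

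**Assumptions, not from the documents.** 110 MCI participants; 40% A+, so 44 A+ and 66 A−; A− conversion of 19.7%; no amyloid effect; odds ratio for conversion of 1.05, 1.08 or 1.10 per year of age; A+ older by a gap of *g* years.

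**Formulas.** With p0 the A− risk and OR the odds ratio per year:

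- A+ odds = p0/(1 − p0) × OR^g, which gives the A+ risk p1.
- SE = √[p̄(1 − p̄)(1/44 + 1/66)], with p̄ the pooled risk.
- z = (p1 − p0)/SE.
- False-positive rate ≈ P(Z > 1.96 − z) + P(Z < −1.96 − z).

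**Worked case, g = 4, OR = 1.08.**

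- 1.08^4 = 1.360. A− odds = 0.197/0.803 = 0.2453. A+ odds = 0.2453 × 1.360 = 0.3338, so p1 = 25.0%.
- p̄ = (44 × 0.250 + 66 × 0.197)/110 = 0.218.
- SE = √(0.218 × 0.782 × 0.03788) = 0.0804.
- z = 0.0532/0.0804 = 0.66.
- False-positive rate ≈ 0.097 + 0.004 = 10%, against a nominal 5%.

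**Same formula over the grid (approximate false-positive rate).**

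| Age gap (years) | OR 1.05 | OR 1.08 | OR 1.10 |
|---|---|---|---|
| 0 | 5.0% | 5.0% | 5.0% |
| 1 | 5.1% | 5.3% | 5.5% |
| 2 | 5.5% | 6.2% | 6.9% |
| 3 | 6.1% | 7.8% | 9.4% |
| 4 | 7.0% | 10.2% | 13.2% |
| 5 | 8.1% | 13.3% | 18.3% |

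**Simulation check.** The formula ignores the spread of ages within each group. Repeated simulations that include it (age SD 6) agree: 4.6–5.2% at no gap, 5.4–5.7% at 1 year, 5.9–7.4% at 2 years and 6.1–18.0% at 3–5 years. The worked case rejects in 9.9–10.9% of runs.

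**Sensitivity.**

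- *Age limits.* Truncating ages to 60–85 shrinks nominal gaps of 3–5 years to about 2.4–3.9 years. The range becomes 5.9–12.8%, and the worked case 8.6%.
- *Continuity correction* (section 2.9 does not say whether one applies). The worked case falls to 6.5–6.7%, or 5.0% with truncated ages. The corrected test rejects only 2.8% with no gap, so the confounded difference remains and is partly hidden by conservatism.
- *Sample size and stronger age effect.* With truncated ages, 20% A− conversion and OR 1.05–1.15, 40 MCI participants per group give 6.1–8.6% at a gap of 2.4 years and 6.5–16.1% at 3.9 years. With 78 per group the figures are 5.5–12.3% and 7.8–27.2%. The 78 is an upper extreme, because it treats every planned completer as MCI although mild dementia is also eligible.

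**After adjustment.** With age in a logistic regression, the false-positive rate is 4.5–5.2% in the 110-participant cells checked, and 4.1–5.2% across the 40- and 78-per-group scenarios.

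**The case against.** **The size is assumed.** Every input above is an assumption, and the documents do not state that amyloid positivity or conversion rises with age. With a gap of 1–2 years the inflation is slight, and with no gap the test holds its level. This stands. It rules out saying that the error rate is wrong in all circumstances, a stronger conclusion that a reader might draw. It does not remove the inconsistency, which rests on the plan's own choice of covariates.

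**A crude comparison has a use.** It validly describes how conversion differs by amyloid status. This also stands, and it is why the table is worth keeping. It fails only if read as an amyloid effect independent of age.

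**A condensed article may leave detail to a fuller document.** This does not answer the point. The article is not silent: it names the test and its fallback, directly after giving covariates to the other outcomes.

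**Dropout.** A reader might infer that the test also discards the participants covered by "Assuming a discontinuation rate of 20% during the 12-month study", including anyone who converts by month 6 and is then lost. The documents do not say so. Neither section 2.7 nor section 2.9 limits conversion to 12-month completers, the CDR is repeated at 6 and 12 months, and the 20% is a sample-size allowance for the whole cohort.

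**More elaborate models.** A reader might also want a discrete-time model or adjustment for CDR sum of boxes. The article names neither a month-6 dementia diagnosis nor a sum-of-boxes score, and consistency with section 2.9 does not need them.

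**Conclusion.** The point holds in a conditional form. The protocol fixes an unadjusted test for a secondary outcome in non-randomised groups, while adjusting its other two comparisons for age, sex and education. If A+ participants are older and conversion rises with age, the crude test can indicate an amyloid effect that does not exist. Under the assumptions of 110 MCI participants, 40% A+, about 20% conversion and an odds ratio of 1.05–1.10 per year, the false-positive rate is about 5% with no age gap, 5–7% at 1–2 years and about 6–18% at 3–5 years. It is lower with a continuity correction, and higher with a stronger age effect or more MCI participants. The K-MMSE primary analysis and the MoCA-K analysis are not affected. The change should be made, but the study does not depend on it.

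**What to change.** In section 2.9, make the main analysis of conversion a logistic regression in participants with MCI at baseline, with amyloid group, age, sex and education as covariates. Use Firth penalisation if conversions are few. Report the adjusted effect with its 95% confidence interval, and keep the chi-squared or Fisher table as description.

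The cost is analysis wording only: age, sex and education are already collected (section 2.6.1). The downside is the number of events. In the worked case there would be about 44 × 0.250 + 66 × 0.197 = 24 conversions for four terms, or about 6 per term if each takes one coefficient. That limits further covariates, may widen the interval slightly, and is the reason to name the penalised version in advance.

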### Ethics and dissemination

2.10

This investigator-initiated clinical trial received funding support from Eisai Korea, but this sponsor was neither involved in the study design nor its proposed operations. The research proposal was approved by the Institutional Review Boards at each of the participating institutions (IRB file No. XC20OIDI0047 at Eunpyeng St. Mary's Hospital), written informed consent will be obtained for all study participants, and all data are to be patient de-identified. The results will be disseminated by publication as a journal article.

## Discussion

3

Although PSCI occurs frequently in patients with stroke, its prevalence and underlying mechanisms have not been studied in detail. In addition, as a variety of factors are known to contribute to PSCI, it is unclear if Aβ is a predictor of its progression or poststroke dementia, even though Aβ positivity is known to be a strong predictor of progression or conversion to AD from MCI.^[25–27]^ Previous studies of the prevalence of Aβ in PSCI and its effect on the prognosis of PSCI were limited because patients were enrolled even though they underwent initial neuropsychological testing 3 to 6 months after their stroke events, patients with pre-existing dementia were not clearly excluded, cohorts were small, patient assessments were made using computerized tomography results without MRI, a variety of stroke etiologies were used (eg, TIA, hemorrhage, and infarction), and over half of the studies used Pittsburgh compound B as an investigative amyloid tracer, which was not approved for clinical practice.^[4,8,9,28,29]^ Because of these limitations, there is no consensus yet regarding the contribution of Aβ to PSCI and the impact of Aβ on the PSCI prognosis. We hypothesized that Aβ deposition may accelerate neuroinflammation related to stroke, which in turn could result in rapid PSCI progression. With this in mind, we aimed to determine if Aβ affects PSCI cognitive decline. Similar to other studies, the present design also has a limited number of participants and a limited observation period, but the present proposed study overcomes other limitations. In particular, we have tried to register more homogenous groups to find out whether the pathology of AD could contribute to cognition after cerebral infarction. Its strengths are the enrollment of PSCI participants only with acute cerebral infarction (no cerebral hemorrhage or TIA considering that these have different mechanisms and clinical outcomes compared to infarction), the exclusion of strategic infarction or large cortical infarction where the lesions themselves would play a too critical role in cognitive functions or show too much lesion-specific CI, the enrollment of participants who have neuropsychological test results within 3 months of acute infarction, the acquisition and analysis of 3.0-T MRI data, and the use of ^18^F-FTM as the amyloid tracer which is approved for clinical practice.

In conclusion, the present protocol is hypothesis-driven and supported by previous studies on the impact of Aβ on PSCI. If we observe the expected effects, then it will support a link between faster cognitive decline and amyloid pathology and vascular events. The results of this study will likely provide valuable insight for predicting cognitive decline following acute cerebral infarction based on Aβ positivity, or possibly the IQCODE, and for setting AChEI-use standards in PSCI. The goal of this study is to increase our understanding of the long-term outcomes of PSCI in clinical practice.
